### Study population

The target population of this randomized controlled trial is primary care physicians and their practice personnel. The majority of these personnel completed a 3-year vocational training with a degree (practice assistants). A few practices also employ secretaries, nurses or personnel without a degree, but with on-the-job training. The intervention will address all staff members handling vaccines regardless of their prior training. Practices are eligible if they administer vaccinations and are situated within a 50-km radius of Essen, Germany. All participating physicians and practice personnel will sign an informed consent form.

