*Secondary outcomes* follow international best practices and guidelines:Temperature monitoring - Improvement in temperature monitoring with optimal monitoring defined as electronic or paper-based recording with a minimum of two readings per day for the previous 5.5 months (5 % missing entries allowed). Prior studies indicated that temperature fluctuations without adequate adjustments over time are a main barrier to intervention success. To overcome this barrier, this intervention program will emphasize temperature monitoring, including temperature reviewing, recording, taking immediate action if needed and retention of temperature logs.Refrigerators not freezing - The proportion of practices with vaccine vials not reaching critically low temperatures (-0.5 °C or lower) will be determined.Compliance with storage recommendations - Improvement in actual refrigerator-related storage quality will be assessed at practice level according to the following examples:Refrigerator is used exclusively for vaccine storage.Standard thermometer is located in refrigerator.No vaccines are stored in refrigerator door.Vaccines are stored in their original wrapping.e Vaccines are stored in the center of the refrigerator.Use of a stock management system (for example, “earliest expiry first out (EEFO)” principle) and regular manual stock control.4.Knowledge about vaccine storage - Improvement in knowledge of good vaccine storage conditions in physicians and practice personnel will be studied using a standardized questionnaire.5.Assignment of personnel - During the initial practice visit the study assistant will ask if practices currently have assigned personnel as vaccine storage manager and backup. This is considered an important structural characteristic to maintain long-term changes at practice level.

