#### Self-administered questionnaire (knowledge and temperature monitoring)

The questionnaire will consist of a knowledge part (part 1) and a part addressing current structures and procedures used for monitoring of temperatures (part 2). The knowledge part will be developed drawing on the international body of recognized best practices and guidelines (for example, WHO), official checklists used in other countries (UK, US, and AUS) and previous studies (for example, [12, 14, 16, 17, 20]). Items will correspond to the five educational topics detailed above. In addition, sociodemographic characteristics of physician and practice personnel (sex, age, years in practice/job, part-/full-time, and job content) and practice characteristics (single/group, number of physicians/medical assistants in practice, number of patients quarterly, average number of vaccinations daily, age structure of patients, and urban/rural) will be included. In part two, the current structures and procedures used for the monitoring of temperatures will be obtained. Participants will complete part 1 and 2 of the questionnaire after accessing the web-based program, but before starting with the educational program itself (t1). Follow-up measurements will use a paper-based version of part 1 of the questionnaire, handed out and collected when downloading follow-up data logger readings (t2 and t4). Inspections of temperature logbooks at t2 and t4 will serve as the follow-up measurement for part 2.

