#### Randomization

Based on results of the temperature baseline data collection, practices with temperatures outside the target range will be randomized equally to the two study arms (1:1). The randomization procedure is computer-based through www.random.org. No participant will be informed about the study hypotheses in detail.

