#### Sample size estimation

The intervention study will be performed in a sample of 46 primary care practices (23 practices per arm) with suboptimal temperature readings at baseline during a 7-day monitoring period (t0). A sample size of 23 practices per group provides an 80 % power to detect anticipated differences between the groups at a significance level of 0.05 %. We assume that 70 % of the practices in the intervention group will reach the temperature target range at follow-up. This assumption is based on two intervention studies of comparable intensity that observed optimal storage conditions in 83 % and 77 % of previously suboptimal practices, using continuous temperature readings as the outcome [18, 19]. Regarding the control group, we expect that 30 % of practices will reach the temperature target range at follow-up due to a study participation effect because of being exposed to temperature monitoring via data logger. This assumption is based on an intervention study that observed optimal temperature readings in 33 % of the control group at follow-up [18].

Owing to the lack of intervention studies available, the power calculation is based on more conservative assumptions.

As the intervention will only be conducted in practices with suboptimal temperatures, a total of 174 practices will have to be recruited for t0. This is based on the assumption that 33.3 % of refrigerators will be outside the target range (n = 58). This percentage is derived from the abovementioned prospective feasibility study in 17 primary care practices with 21 vaccine refrigerators and similar results reported by Bell et al. (2001), Jeremijenko et al. (1996) and Lewis et al. (2001) [14, 18, 20]. Our calculation takes into account a dropout rate of 20 %. This dropout rate is based on our experience and corresponds to reports from other cluster-randomized trials [24]. Using an adaptive design, baseline temperature measurements for t0 will be stopped as soon as the anticipated total sample of n = 58 is reached.

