### Statistical analysis

Descriptive statistics will be used to describe baseline characteristics for both study arms with regard to practice characteristics (single/group, number of physicians/medical assistants in practice, number of patients quarterly, average number of vaccinations daily/per week, age structure of patients), participating physician and practice personnel characteristics (sex, age, years in practice/job, part-time/full-time, job content). The effectiveness will be assessed by comparing the intervention and control group and by intragroup comparison (baseline versus follow-up). We will evaluate the effectiveness based on temperature as the main outcome (within range yes/no) by comparing both groups using the chi-square test. For intergroup analyses, all dichotomous secondary outcomes will be evaluated using chi-square tests for each item. In addition, compliance with storage recommendations will be analyzed on the basis of a sum score calculated across all items by using a t-test. For in-group comparisons, McNemar tests will be calculated for dichotomous outcomes and t-tests for dependent samples for sum scores. Temperature monitoring will be measured on an ordinal level to allow for application of the Mann-Whitney U Test (intergroup comparison) and the Wilcoxon signed rank sum test (intragroup comparison). A *P* value <0.05 will be considered significant. All statistical analyses will be performed using IBM SPSS 22® on Windows.

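### Knowledge is collected from individual staff within randomised practices, but the stated tests make no allowance for practice, so person-level analysis would exceed the nominal 5 % error rate

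*Protocol article*

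**What the plan says.** All places are in the protocol article.

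- **Unit of allocation.** The Randomization section assigns whole practices: "practices with temperatures outside the target range will be randomized equally to the two study arms (1:1".
- **Unit of measurement for knowledge.** Outcomes, fourth secondary outcome: "Improvement in knowledge of good vaccine storage conditions in physicians and practice personnel will be studied using a standardized questionnaire". Study population: "The intervention will address all staff members handling vaccines regardless of their prior training". The section on the self-administered questionnaire records each respondent's own characteristics, such as sex, age and years in the job. It repeats the knowledge part at t2 and t4: "Follow-up measurements will use a paper-based version of part 1 of the questionnaire".
- **Between-group test.** Statistical analysis: "For intergroup analyses, all dichotomous secondary outcomes will be evaluated using chi-square tests for each item". The sum score with a t-test that follows is named for storage compliance only.
- **Within-group tests.** Statistical analysis: "For in-group comparisons, McNemar tests will be calculated for dichotomous outcomes and t-tests for dependent samples for sum scores".
- **Threshold.** A P "value <0.05 will be considered significant".
- **Clustering.** The analysis section mentions no practice effect, aggregation to practice level, mixed model, GEE or robust standard error. The only reference to clustering is in Sample size estimation, where the assumed dropout rate "corresponds to reports from other cluster-randomized trials".

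**The concern.** An ordinary chi-square test assumes independent observations. Colleagues in one practice share a refrigerator, routines and a storage manual, and the programme deliberately acts on the practice as an organisation as well as on the individual. Their answers to the same knowledge item are therefore likely to be correlated. When whole practices are allocated, that correlation inflates the variance of the difference between arms. A test that ignores it uses a standard error that is too small, and its P values are too small as well.

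Knowledge is what an education programme acts on most directly. An arm difference in knowledge declared significant on this basis would be supported less well than its P value suggests.

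**Working it through.** **1. The plan's own figure, to fix the scope.** The sample size concerns practices: 70 % against 30 % in range, 80 % power. I take alpha as 5 % two-sided, in line with the analysis section; the sample size section prints 0.05 %.

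n per arm = [1.96 × √(2 × 0.5 × 0.5) + 0.8416 × √(0.7 × 0.3 + 0.3 × 0.7)]² / 0.4² = (1.386 + 0.545)² / 0.16 = 23.3, rounded up to 24.

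At the planned 23 per arm, power is 79.4 % by the normal approximation and 80.9 % by exact enumeration of the uncorrected chi-square test. Dropout: 46 / 0.8 = 57.5, so 58. The plan's figures reproduce to within one practice per arm. They rest on one refrigerator per practice, so clustering of staff does not enter.

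**2. Which outcomes have several observations per practice.**

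| Outcome | Source | Observations per practice |
|---|---|---|
| Temperature in range (primary) | one logger in one selected refrigerator | one |
| No critically low temperature | same logger | one |
| Storage compliance | checklist by the study assistant | one |
| Temperature monitoring at follow-up | inspection of the logbook | one |
| Assignment of personnel | question to the practice | one |
| Knowledge | questionnaire to physicians and personnel | potentially several |

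**3. Error rate of an unadjusted test on knowledge.** Inputs: 23 practices per arm and a nominal 5 % level (article); respondents per practice, m, and the ICC (both assumed).

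- Design effect: DE = 1 + (m − 1) × ICC.
- Actual two-sided type I error: 2 × [1 − Φ(1.96 / √DE)].

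Example with m = 5 and ICC = 0.10: DE = 1 + 4 × 0.10 = 1.40; 1.96 / √1.40 = 1.656; type I error = 9.8 %.

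The formula was checked by beta-binomial simulation (23 practices per arm, 50 % correct in both arms, 20,000 replicates, rejection above 3.84):

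| m | ICC | DE | Formula | Simulation |
|---|---|---|---|---|
| 3 | 0.05 | 1.10 | 6.2 % | 6.3 % |
| 3 | 0.10 | 1.20 | 7.4 % | 7.4 % |
| 3 | 0.20 | 1.40 | 9.8 % | 9.6 % |
| 5 | 0.05 | 1.20 | 7.4 % | 8.1 % |
| 5 | 0.10 | 1.40 | 9.8 % | 10.6 % |
| 5 | 0.20 | 1.80 | 14.4 % | 15.2 % |

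With m = 2 and ICC 0.05, DE is 1.05 and the error only 5.6 %. With one respondent per practice there is no inflation.

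**4. Does accounting for practice repair it?** In a separate simulation of 40,000 runs (m = 3, 4 and 6; ICC 0.05 to 0.30), a t-test on practice proportions held the type I error at 4.9 to 5.2 % throughout.

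**5. Within-group tests.** McNemar and paired t-tests on individuals also ignore practice. What matters there is the within-practice correlation of changes, a different quantity from the ICC above. If it is positive, the direction is the same; its size was not computed.

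**The case against.** The strongest counter-argument is that the Statistical analysis section never names knowledge. The sentence on item-wise chi-square tests is followed by one on a storage-compliance sum score across all items, so its items may chiefly be those of the storage checklist, which is assessed per practice. The article does not say whether knowledge items are scored right or wrong, or whether the analysed unit is the person or the practice. This stands as a limit: applying the chi-square test to knowledge is an inference from the sentence covering all dichotomous secondary outcomes. It does not remove the point. No other between-group test in the article covers knowledge, and an ordinary t-test on individual scores would have the same fault. The analysis section states specific unadjusted tests; this is not merely a detail left to another document.

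A reader might also infer more than the article supports:

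- **That the trial's main result is compromised.** It is not. Effectiveness is defined by refrigerator temperature, with one observation per practice.
- **That several false item-level effects are likely.** The number of items is not given. With, say, 10 items and a 6.3 % error rate, about 0.63 false positives are expected, against 0.5 nominally.
- **That the plan passes over an available total knowledge score and must test only that.** No such score is defined. A single summary test is a preference, and item-level reporting of a secondary outcome is not an error.
- **That the authors have declared a cluster analysis and then ignored it.** The reference to cluster-randomised trials supports a dropout rate. It suggests they see the design as clustered, but says nothing about the analysis.

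Finally, the size rests on assumptions. With few respondents and a low ICC the inflation is small.

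**Conclusion.** The point holds for knowledge only. If knowledge is analysed per person with the tests stated, the between-group type I error exceeds 5 % whenever practices contribute more than one respondent and the ICC is positive. Taking the formula and the simulation together, it is about 6 to 10 % with 3 respondents per practice and about 7 to 15 % with 5, for ICC 0.05 to 0.20. The direction does not depend on the values assumed; the size does. Severity is moderate: one of five secondary outcomes is affected, and neither the primary comparison nor the sample size changes.

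**What to change.** In the Statistical analysis section, name the unit of analysis for knowledge and account for practice in one of two ways:

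- **Practice-level summaries:** a t-test or ANCOVA on each practice's mean score or proportion correct, adjusted for the practice's baseline value.
- **Individual-level model:** a mixed model or GEE with practice as the cluster and a small-sample correction, since there are only 23 practices per arm.

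Within-group comparisons of knowledge should follow the same choice. The tests for the other outcomes can stay as far as clustering is concerned.

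No new data are needed, only that questionnaires can be linked to their practice. Recruitment had not begun when the article was written. The cost is a little more analysis work and wider intervals, by a factor of about √DE: √1.10 = 1.05 to √1.40 = 1.18 with 3 respondents, and √1.20 = 1.10 to √1.80 = 1.34 with 5, over the same assumed ICC range.

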## Discussion

To our knowledge, this will be the first randomized controlled trial evaluating a web-based approach in comparison to a control group addressing the issue of vaccine storage. The topic is important to ensure vaccine effectiveness and safety but currently plays a minor role, at least in German primary care practices. Some of this lack of recognition is due to the fact that this topic is only marginally addressed, if addressed at all, in the medical education of physicians and practice personnel.

Effectively changing medical practice requires a “complex approach focused on different levels, tailored to specific settings and target groups” [21]. To address the issue of vaccine storage, we chose a web-based education that combines a number of benefits. First, while being as effective and satisfactory as traditional educational approaches [25, 26], it addresses both target populations, that is, physicians and practice team members. The tailored presentation of relevant learning content is discussed to increase the appropriateness of the information on a personal level, thereby implying that contents are better remembered and more frequently discussed (for example, [27]). Although computer tailoring has not been studied in healthcare providers, it was proven to be effective in patients’ health education and promotion [28, 29]. Second, an e-learning intervention tool can easily be used for recurrent training, for example, to train new personnel in case of fluctuation or to retrain staff in the form of continuous medical education. Third, in contrast to 1:1 education our web-based learning format can be disseminated on a larger scale at low cost.

Methodologically, the study exhibits a number of strengths. First, in contrast to prior studies, continuous vial temperature using a glycol probe as opposed to single-point measurements of ambient air temperature is used as a primary outcome parameter. Second, to take into account the frequently reported fluctuations in performances, several strategies to intensify the intervention are combined: the intervention is directed at both the individual physician and practice personnel as well as the organizational level. Participants will receive tailored information and a manual for later reference, whereas the practice as an organizational unit will receive managerial support in the form of templates, plans and guides for various aspects of vaccine management, for example, for temperature recording and emergency plans in the event of equipment failure. A manual on vaccine storage management is a novelty to German practices as currently no agreed-upon reference is available, and the official German recommendations for vaccines contain only little information on storage issues. Third, in contrast to some prior interventions lacking in-depth descriptions of intervention contents and implementation processes, we will describe the content of the web-based education intervention in detail to allow for replication and/or building on research findings. Fourth, our web-based intervention is designed for future widespread use in small and larger healthcare institutions at low cost.

## Trial status

Practice recruitment is planned to start in January 2016.

## Abbreviations

AUS: Australia
C: Celsius
CDC: Centers for Disease Control
F: Fahrenheit
UK: United Kingdom
US: United States of America
WHO: World Health Organization
